## Abstract

•This protocol describes a multicentre, randomized, placebo-controlled trial that aims to assess the efficacy and safety of specific stimulation mode SMES combined with NGF in reducing the recovery period of ischaemic stroke and provide evidence-based medical data.•This research will help provide the latest and high-quality evidence for clinicians and policymakers seeking innovative and effective ways to treat patients with ischaemic stroke.

This protocol describes a multicentre, randomized, placebo-controlled trial that aims to assess the efficacy and safety of specific stimulation mode SMES combined with NGF in reducing the recovery period of ischaemic stroke and provide evidence-based medical data.

This research will help provide the latest and high-quality evidence for clinicians and policymakers seeking innovative and effective ways to treat patients with ischaemic stroke.

## Introduction

A trend towards increasing stroke incidence or mortality rates, in people was recently observed in China.^1^ Ischaemic stroke is a common clinical disease that mainly manifests as limb movement and sensory disorders accompanied by decreased learning and memory ability.^2^ A large number of clinical data show that the ischaemic stroke during convalescence, which ranges from 2-weeks to 6-months after the onset of stroke, is the best time for functional recovery of patients with cerebral infarction.^3^ Therefore, improving the clinical efficacy of stroke treatment during the recovery period after stroke is a widely researched topic of interest in neuroscience.

Nerve Growth Factor (NGF) was the first neurotrophic drug to be discovered; it provides nerve repair and protective effects as well as plays an active role in nourishing nerves, promoting neuronal survival, and inhibiting cell apoptosis.^4^ A recent case report demonstrated that intranasal NGF administration improved cerebral function in a child with severe traumatic brain injury.^5^ Nevertheless, the effect of NGF on patients with ischaemic stroke during convalescence is not satisfactory as the molecular weight of NGF is approximately 13.4 kDa, which makes it difficult for it to cross the Blood-Brain Barrier (BBB) under normal conditions and affects its ability to reach the effective drug concentration to exert therapeutic effect.^6^ Therefore, there is an urgent need to find an effective method through which neuroprotective agents, such as NGF, can safely penetrate the BBB.

Acupuncture is a method that has been employed to treat stroke in China since ancient times and has been widely accepted worldwide.^7^ Specific Mode Electroacupuncture Stimulation (SMES) involves the application of electrical stimulation in which an electric current passes between acupuncture needles.^8^ Previous studies have shown that SMES can be used as a means of opening the BBB. Moreover, our previous study showed that at a frequency of 2/100 Hz, 3 mA SMES (a homemade relay cycled power to the electrode with 6s on-and off-cycle) applied for 40 min at the meridians GV20 (Baihui) and GV26 (Shuigou) can increase the permeability of BBB to NGF.^9^ Our repeated experiments on SD rats revealed that these SMES stimulation parameters were stable and safe for the opening of the BBB; therefore, our research team named it specific stimulation mode SMES.

This study aimed to evaluate the effectiveness and safety profile of specific stimulation mode SMES combined with NGF used in the treatment of ischaemic stroke during the recovery period. The main hypothesis of this trial is that compared to the control groups, the SMES + NGF group will provide remarkably improved motor and cognitive function. Moreover, these improvements will be associated with changes in cerebral blood flow and brain function. Further, this study innovatively combines SMES and NGF to treat patients with ischaemic stroke during convalescence and, thus, will provide a new treatment method with sufficient clinical evidence.

## Methods and analysis

### Study design

This study will be a multicentre, parallel, outcome-assessor-blinded, placebo-controlled, randomized trial consisting of a 4-week treatment phase, followed by a 12-week follow-up phase. Figure 1 displays the trial process, and Table 1 provides details of the trial schedule.

**Fig. 1 fig0001:**
[figure not shown]
Study Flow: Steps that all patients should go through from enrolment to analysis.

**Table 1 tbl0001:** Schedule of enrolment, interventions and assessments.

Stage	Baseline	Treatment phase				Follow-up phase	
Number of visits	1	2	3	4	5	6	7
Time point	Week 0	Week 1±1 day	Week 2±1 day	Week 3±1 day	Week 4±1 day	Week 8±3 days	Week 12±3 days
Eligibility screening	X						
Informed Consent Form	X						
Demographic characteristics	X						
Medical history	X						
Definitive diagnosis	X						
Inclusion criteria	X						
Exclusion criteria	X						
Evaluation of treatment expectation	X						
Therapeutic effect record form		X	X	X	X		
Scale assessment							
Modified Rankin Scale, mRS	X		X		X	X	X
Modified Barthel Index (MBI)	X		X		X		
Simplified Fugl-Meyer Assessment of motor function score (FMA)	X		X		X		
Timed up and go test	X		X		X		
Tinetti Performance Oriented Mobility Assessment (POMA)	X		X		X		
Montreal Cognitive Assessment (MoCA)	X		X		X	X	X
Informant Questionnaire on Cognitive Decline in the Elderly (IQCODE)	X						
Mini-mental State Examination, MMSE	X						
Loewenstein Occupational Therapy Cognitive Assessment (LOTCA)	X		X		X		
Acupuncture safety evaluation		X	X	X	X		
NGF treatment safety evaluation		X	X	X	X		
Adherence assessment					X		
Combination of medications	X						
Adverse Events		X					
Data Processing	X						
Research Completion	X						
Researcher Review	X						

### Setting, recruitment, and participants

This trial will be conducted at the Third Affiliated Hospital of Zhejiang Chinese Medical University, the Ningbo Hwamei Hospital, and the Lishui Second People's Hospital. The recruitment criteria will include:

#### Inclusion criteria

The inclusion criteria include (1) Patients with first-ever ischaemic stroke confirmed by Computed Tomography (CT) and/or Magnetic Resonance Imaging (MRI); (2) 14-days to 6 months after the onset of stroke;(3) Patients between the ages of 30 and 80; (4) Modified Rankin Score (mRS), 3‒4; and Mini-Mental State Examination (MMSE) < 27; (5) Patients who are able to accept and comply with EA treatment and have good compliance; (6) A willingness to participate in the project.

#### Exclusion criteria

The exclusion criteria are: (1) Transient ischaemic attack, cerebral haemorrhage, and other cerebrovascular diseases; (2) Unstable medical condition (e.g., patients in the intensive care unit, myocardial infarction, severe pulmonary disease); (3) Brain tumours, cerebral infarction caused by repeated recurrence of stroke and brain surgery or trauma; (4) Visual or auditory impairment, aphasia, agnosia, severe hemiplegia, or affected limb function before stroke; (5) Deficiencies in cognitive function prior to stroke, such as alcoholism, drug abuse and congenital dementia, Informant Questionnaire on Cognitive Decline in the Elderly (IQCODE) ≥ 3.19; (6) Women who are lactating, pregnant or intending to get pregnant; (7) Skin infection at acupuncture site, needle sickness, or needle phobia; (8) Implantable cardioverter defibrillator carriers, conductive metallic foreign bodies in the body, or a pacemaker; (9) Allergic after using NGF; (10) Participated in clinical trials three months ago or currently in other clinical trials.

### Randomization and allocation concealment

Patients who qualify for inclusion will be recruited from March 2022 to December 2025. The recruited participants will be randomly divided into four groups by a randomization system (eBalance, Randomization and Trial Supply Management, Taimei Technology, Shanghai, China) and allocated to four groups, namely: acupuncture + placebo, acupuncture + NGF, SMES + placebo, and SMES + NGF groups.

### Blinding

In this trial, it will be difficult to blind the researchers because they will perform SMES or acupuncture procedures and inject NGF or placebo into patients. Throughout the trial, patients, independent statisticians, and independent outcome assessors will be unaware of the group allocation data.

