### Interventions

#### Acupuncture intervention

The patient lay in a supine position, after disinfection of acupoint skin, two stainless steel needles (Hua Tuo brand, Suzhou Medical Supplies Company Ltd., Jiangsu, China) of sizes 0.25 × 40 mm and 0.25 × 25 mm, will be inserted into the GV20 (Baihui) and GV26 (Shuigou), respectively (Fig. 2). The acupoints will be stimulated manually until the patients feel distension, heaviness, or soreness.

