#### SMES intervention

On the basis of the above acupuncture, add the electroacupuncture instrument (HANS-200, Nanjing Jinsheng, Ltd., China) to connect the acupuncture needle with an intensity of 3 mA and a frequency of 2/100 Hz for 40 min (a self-made relay cycled power to the electrode for 6s on and off).

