#### Study flow and treatment procedure

NGF or placebo will be injected into the gluteus maximus and followed by either SMES or acupuncture for 40 min.

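### Patient blinding is claimed for allocation as a whole, but the procedures described can blind patients only to NGF versus placebo, not to SMES versus acupuncture

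*Protocol article*

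**What the plan says.** The Blinding section makes a positive statement about three parties: "Throughout the trial, patients, independent statisticians, and independent outcome assessors will be unaware of the group allocation data". The same section excepts the treating staff, saying that "it will be difficult to blind the researchers because they will perform SMES or acupuncture procedures and inject NGF or placebo into patients".

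The arms, under Randomization and allocation concealment, are "acupuncture + placebo, acupuncture + NGF, SMES + placebo, and SMES + NGF groups", a two-by-two layout of procedure (acupuncture or SMES) by injection (placebo or NGF).

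Under Acupuncture intervention, needles are placed at two points and worked by hand: "The acupoints will be stimulated manually until the patients feel distension, heaviness, or soreness". Under SMES intervention, the device is an addition to that procedure: "On the basis of the above acupuncture, add the electroacupuncture instrument", which is used "to connect the acupuncture needle with an intensity of 3 mA and a frequency of 2/100 Hz for 40 min", with the current switching on and off in 6-second cycles. Study flow and treatment procedure gives the session order: "NGF or placebo will be injected into the gluteus maximus and followed by either SMES or acupuncture for 40 min".

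Study design describes the trial as a "multicentre, parallel, outcome-assessor-blinded, placebo-controlled, randomized trial". Outcome assessors are named there; patients are not.

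**The concern.** The Blinding section and the intervention sections cannot both stand as written. A patient in an SMES arm is connected to an electrical instrument for 40 minutes per session. A patient in an acupuncture arm, by the description given, is not. The only placebo named is the one for NGF, and it does nothing to hide whether a device is attached.

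What is at stake is how the results may be described. The Introduction states the main hypothesis as SMES + NGF against the control groups, in the plural. One of those comparisons, against acupuncture + NGF, bears directly on the rationale that SMES helps NGF cross the blood-brain barrier. If the blinding sentence is carried into the report unchanged, readers will take a difference in that comparison as protected from patient expectation, which the described design does not provide. Blinded assessors protect the ratings in part, but a patient who knows whether a device was used can disclose it.

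**Working it through.** No arithmetic decides the main point. The check sets the sections side by side and then counts the comparisons affected.

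**Step 1: what a patient meets in each session** (Acupuncture intervention, SMES intervention, Study flow and treatment procedure)

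- Injection: all four arms receive one, NGF or placebo.
- Needles at GV20 and GV26: all four arms.
- Session length: 40 minutes for SMES or acupuncture.
- Connected instrument with current at 3 mA, 2/100 Hz, 6 s on and off: the two SMES arms only.
- Dummy instrument, unpowered leads or other masking in the acupuncture arms: none described.

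The injection, the needle sites and the session length are matched. The device is not. The Inclusion criteria also require every patient to be able to accept electroacupuncture, so patients can be expected to know that an electrical procedure is one of the possibilities.

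**Step 2: the three comparisons in the main hypothesis** (Introduction; arms from Randomization and allocation concealment)

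- SMES + NGF vs SMES + placebo: differs in the injection only. Patient blinding is possible as described.
- SMES + NGF vs acupuncture + NGF: differs in the device only. Patient blinding to that difference is not supported.
- SMES + NGF vs acupuncture + placebo: differs in both. Patient blinding to the device part is not supported.

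So 2 of the 3 control comparisons cross the device difference.

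**Step 3: which comparison the sample size rests on** (Sample size calculation)

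The formula is applied with PT = 75% and PC = 50%, which are the rates given for SMES + NGF and SMES + placebo. With two-sided α = 0.05 (the article does not state sidedness) and power 0.80:

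n = (1.960 + 0.842)² × [0.50 × 0.50 + 0.75 × 0.25] / (0.75 − 0.50)² = 7.849 × 0.4375 / 0.0625 = 54.94, rounded up to 55.

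This reproduces the stated 55 per group. The planned size therefore belongs to the one comparison that the device difference does not touch.

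**The case against.** The strongest reply has four parts.

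*The article is condensed, and a sham set-up may be in the full protocol.* This cannot be excluded. But the point is not that a detail is absent. The article makes a positive claim about patients, and its own account of the procedures, in which the instrument is an addition to acupuncture, runs against it. If masking exists, one sentence resolves the matter.

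*No patient can know their full group.* This stands. A reader might infer that the two comparisons are open-label to the patient. The documents do not support that: every patient receives an injection of NGF or placebo, and feeling current does not reveal which. The exact statement is that patients are not blinded to SMES versus acupuncture. Even this is an inference from the procedures, since the article reports nothing on whether the current is perceived.

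*The route to the primary outcome is not shown.* This also stands. A reader might infer that the primary result will be collected by telephone from unblinded patients. Under Follow-ups, telephone and home contact apply only to the visits after treatment. At week 4 the mRS is repeated alongside the clinical examinations, and the article does not say which time point is primary. Assessors are stated to be blinded, and both procedures involve active needling, so even the direction of an expectation effect is an assumption. One can assume a shift in the rate of mRS ≤2 and derive an inflated false-positive rate, but the shift would be invented. An assumption about borderline patients would also have to be scaled by their share of the arm, which the article does not give.

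*The injection side is sound as far as can be seen.* A reader might infer from the remark on researchers that injecting staff know every allocation and that the SMES + NGF vs SMES + placebo comparison is compromised too. The article says only that blinding them will be difficult. How NGF and placebo are labelled and supplied, and whether patients are asked to guess their allocation, are details that an article commonly leaves to the full protocol. Neither is a finding here.

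**Conclusion.** The statement on patient blinding is wrong as written, in a limited way. The described design can blind patients to NGF versus placebo. It does not blind them to SMES versus acupuncture. Two of the three control comparisons in the main hypothesis are therefore not patient-blinded for the device factor, while the comparison behind the 55 per group is unaffected.

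The conclusion rests on two assumptions: that the intervention sections describe the acupuncture arms completely, with no device attached, and that a patient can notice being connected to an instrument delivering 3 mA for 40 minutes. It does not rest on any estimate of bias. The documents contain none, and it should not be read as showing that the primary result will be biased.

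**What to change.** Reconcile the Blinding section with Acupuncture intervention, SMES intervention, and Study flow and treatment procedure, in one of two ways:

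1. If the device is masked in the acupuncture arms, say how.
2. If it is not, limit the patient-blinding claim to the NGF or placebo injection. Then label SMES + NGF vs acupuncture + placebo and SMES + NGF vs acupuncture + NGF as not patient-blinded to the device wherever conclusions are drawn from them.

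The label in Study design, which names only the outcome assessor, already fits the second option and needs no change.

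The cost is a few sentences and a less favourable blinding claim. A zero-output dummy unit in the acupuncture arms is a possible further step, but this point does not depend on it. It would only partly mask a current that patients can feel, and with recruitment dated March 2022 to December 2025 it could change the control procedure partway through the trial.

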### Interventions

#### Acupuncture intervention

The patient lay in a supine position, after disinfection of acupoint skin, two stainless steel needles (Hua Tuo brand, Suzhou Medical Supplies Company Ltd., Jiangsu, China) of sizes 0.25 × 40 mm and 0.25 × 25 mm, will be inserted into the GV20 (Baihui) and GV26 (Shuigou), respectively (Fig. 2). The acupoints will be stimulated manually until the patients feel distension, heaviness, or soreness.

**Fig. 2 fig0002:**
[figure not shown]
Location diagram of GV20 (Baihui) and GV26 (Shuigou).

#### SMES intervention

On the basis of the above acupuncture, add the electroacupuncture instrument (HANS-200, Nanjing Jinsheng, Ltd., China) to connect the acupuncture needle with an intensity of 3 mA and a frequency of 2/100 Hz for 40 min (a self-made relay cycled power to the electrode for 6s on and off).

#### NGF injection

A 20 µg NGF (n° S20060051, Jinlujie, Hiteck Biopharmaceutical Co., Ltd., Wuhan, China) will be dissolved in 2 mL sterile water for injection. Patients will receive intramuscular injection of gluteus maximus once a day, 28 days a course of treatment according to the instructions.

#### Study flow and treatment procedure

NGF or placebo will be injected into the gluteus maximus and followed by either SMES or acupuncture for 40 min.

#### rs-fMRI

A reasonable number of acupuncture + NGF and SMES + NGF (i.e., 20) will be selected. These patients will then undergo an rs-fMRI examination using a 1.5T MRI scanner (uMR586, Shanghai Lianying Medical Technology Co., Ltd., China). Patients will be required to remain still, close their eyes, remain awake and relaxed, and minimize their thoughts.

The resting-state rs-fMRI will sequence for obtaining Blood-Oxygen-Level Dependent (BOLD) and Three-Dimensional T1-Weighted Imaging (3D-T1WI). After data processing, the values of the Amplitude of Low-Frequency Fluctuations (ALFF), Regional Homogeneity (ReHo), and Functional Connectivity (FC) will be calculated to observe changes in brain function.

#### fNIRS

Each group will select a sample size of 10 patients with infarct lesions on the left side. The fNIRS examination will be conducted using the LIGHTNIRS device manufactured by Shimadzu in Kyoto, Japan.

Patients will perform three tasks sequentially: cognitive, upper limb movement, and lower limb movement tasks. The interval between tasks will be 2 min. The Cognitive task requires completing the Stroop task, an event-related design using E-prime 3.0 (Psychology Software Tools Inc., Pittsburgh, PA, USA).^10^ The upper-limb movement task consists of clench tasks (10 times) with a disabled hand. Lower limb movement tasks include bilateral hip joint exercises (10 times) using a mechanical pedal. Each task comprises 15s of movement execution and 15s of rest.

After data collection, fNIRS data will be pre-processed and analyzed using the Metlab 2020b (MathWorks Inc., Natick, Massachusetts, United States).^11^

### Outcome measures and evaluation

The primary outcome measure will be the basic cure rate (patients with mRs ≤2 are judged as clinically cured; basic cure rate = number of participants in a group with mRs ≤2/total participants in group × 100%).^12^ The mRs score was 0‒6 points. The higher the score, the more serious the neurological deficit. The secondary outcome indicators are FMA, MBI, TUGT, POMA, MoCA, LOTCA.

Baseline data will be collected by an independent outcome evaluator on the first visit (week 0), including participants' demographic data, medical history, comorbidities, major medications, and clinical evaluation, including ECG, routine blood/urine/stool tests, electrolytes, liver/renal function examinations, as well as mRs, FMA, MBI, TUGT, POMA, MoCA, and LOTCA. At the end of treatment (week 4), patients will undergo the above examinations again and subsequently enter the follow-up period.

### Follow-ups

All participants in the four groups will be contacted either through outpatient, home visit, telephone, or other forms of communication according to the different physical conditions of the patients by the same outcome assessor at 4- and 8-weeks after the trial. The outcome assessor will use the mRs and MoCA scales to assess patients' conditions during the follow-up phase.

### Safety assessment

All patients will be requested to report Adverse Events (AEs) that occur during the trial. AE details, including duration, severity, measures taken, and outcome, will be recorded in Case Report Forms (CRFs). The relationship between the intervention and AEs will be assessed according to the WHO Uppsala Monitoring Centre System for standardized case causality assessment.^13^ If patients develop a severe AE (SAE) related to SMES or NGF during the trial, they will immediately obtain medical help and be allowed to drop out of the trial. Severe Adverse Reactions (SARs) or SAEs are defined according to the International Conference on Harmonisation Tripartite guidelines and will be reported to the ethics committee of the Third Affiliated Hospital of Zhejiang Chinese Medical University and the research team.^14^

### Data collection, management, and monitoring

Patients' information, results from the scores' evaluation, laboratory examination, and other relevant data will be collected at baseline (week 0), post-treatment (week 4), and follow-up assessments (weeks 4 and 8 after the trial). AEs will be observed and recorded from the baseline to the final follow-up. The data will be entered into a pre-designed database by two independent investigators. The data entered will be scrutinized by another researcher to ensure accuracy.

### Sample size calculation

Based on our earlier randomized controlled pre-study, the authors use The basic cure rate as the baseline for the sample size calculation for the present work; the rate of acupuncture + placebo, acupuncture + NGF, SMES + placebo, and SMES + NGF groups were 35%, 40%, 50%, and 75%, respectively.to observe the difference in the basic cure rates between the 4 groups of cases were distributed in proportion of 1:1:1:1, setting the significance value as 5% (α = 0.05), and the test efficiency with 1-β = 0.8. Four groups of samples were calculated, with at least 55 samples in each group. Considering the existence of factors, such as shedding and loss to follow-up, the sample size was expanded by 20%. Finally, the sample was expanded to 288 cases. The sample size estimation formula used is as follows (here PT = 75%, PC = 50%): $n=\frac{{\left(z_{\alpha }+z_{\beta }\right)}^{2}[p_{c}\left(1-p_{c}\right)+p_{r}\left(1-p_{r}\right)}{{\left(p_{r}-p_{c}\right)}^{2}}$.

